### Measurements

Data on the patients’ medical history, physical examination findings, vital signs, anthropometric measures, blood biochemical tests, and imaging parameters will be collected by trained staff at our institution. Weight and height will be measured by trained nurses, and body mass index will be calculated as the weight in kilograms divided by height in meters squared. Body composition will be assessed using a multifrequency bioimpedance analyzer (InBody 720; InBody, Seoul, Korea) [22].

The primary endpoint of this study is the change in hemoglobin A1c after 24 months of statin treatment. The secondary endpoints include changes in other laboratory variables, such as insulin, C-peptide, the insulin resistance index of the homeostasis model assessment, the insulin secretory ability index of the homeostasis model assessment, lipid profiles (including total cholesterol, triglycerides, high-density lipoprotein cholesterol, and low-density lipoprotein cholesterol), adiponectin, C-reactive peptide, and troponin I, after 24 months of statin treatment. Carotid ultrasound and echocardiography will be performed at baseline and after 12 and 24 months of therapy to obtain data on carotid elasticity and cardiac function, respectively. Specifically, the carotid elasticity metrics, including strain, stiffness, and distensibility by the B-mode and speckle-tracking methods, will be measured as described previously [23]. The imaging parameters of cardiac function to be measured include the left ventricular global longitudinal strain by speckle-tracking echocardiography as well as traditional indices derived from two-dimensional, Doppler, and tissue Doppler echocardiography [24]. Additional file 2 provides a detailed description of the methods that will be used to measure the carotid ultrasound and echocardiographic parameters.

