### Statistical analyses

The statistical analyses will be performed on both intention-to-treat and per-protocol bases. The intention-to-treat analyses will include all randomized participants who provide written informed consent, regardless of whether the study treatment is administered correctly. The per-protocol analyses will include all study participants who complete the trial with an adequate administration of the study drug (≥70% of the planned doses) and without any major protocol violations. Major protocol violations include inappropriate enrollment, the use of a prohibited concomitant medication, a violation of the dose or schedule of drug administration, or any other violation considered to be a major violation. The main analyses will be performed on an intention-to-treat basis.

The values will be expressed as the mean ± SD or median (IQR), as appropriate. Comparisons of continuous and categorical data will be made by Student’s *t* test and the chi-square test, respectively. The difference in changes between the groups will be analyzed using both Student’s *t* test and analysis of covariance to adjust for the baseline values. Two-sided *p* values < 0.05 will be considered statistically significant. All analyses will be performed using IBM SPSS version 22.0 software (IBM, Armonk, NY, USA).

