
Further, adiponectin has gained increasing recognition as an important antidiabetic hormone derived from adipose tissue [10, 41, 42]. Thus, the investigation of the link between statins and adiponectin may help to elucidate the molecular mechanisms underlying statin-induced diabetes. Several previous studies, albeit conducted in small numbers of patients, have demonstrated that the effects of statins on adiponectin differ according to the type of statin used [10]. Of note, in these studies, increases in the plasma adiponectin levels were relatively consistent and almost exclusively observed in patients receiving pitavastatin [43–45], whereas the adiponectin levels were unchanged or even decreased in those treated with other statin types, including atorvastatin [17, 46–48]. These findings suggest that the adiponectin-increasing effect of pitavastatin might be causally related to its neutral or favorable impact on glucose metabolism. The LESS-DM trial results will shed light on the potential link between the statin type and diabetogenicity by assessing the continuous changes in the adiponectin levels and the relationship between these changes and several glucose metabolism parameters. Considering that hypoadiponectinemia is a main contributor to MetS [49–51], patients with MetS are an appropriate study population for assessing the adiponectin-increasing effect of statins. Additionally, some studies have suggested that adiponectin per se may be protective against arterial stiffness [52, 53] and left ventricular systolic dysfunction [54, 55]. Taken together, it can be speculated that the use of statins with positive effects on the adiponectin level might have more beneficial impacts on the vascular and cardiac functions in patients with MetS, as compared with other statins, a hypothesis that will be tested in this trial.

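### One p<0.05 label covers every endpoint, and neither the t test nor ANCOVA is named as the test that decides

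*Protocol article*

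**What the plan says.** The Measurements section fixes one primary endpoint at one time: "The primary endpoint of this study is the change in hemoglobin A1c after 24 months of statin treatment". It then opens a long secondary list: "The secondary endpoints include changes in other laboratory variables, such as insulin, C-peptide" and nine further laboratory variables. The imaging endpoints follow. They are "the carotid elasticity metrics, including strain, stiffness, and distensibility by the B-mode and speckle-tracking methods" and, for the heart, "the left ventricular global longitudinal strain by speckle-tracking echocardiography as well as traditional indices derived from two-dimensional, Doppler, and tissue Doppler echocardiography". The number of traditional indices is not given. The Abstract adds new-onset diabetes (NOD) and cardiovascular disease (CVD) as secondary clinical events.

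The Statistical analyses section sets one threshold for all of these: two-sided p "values < 0.05 will be considered statistically significant". Between-group differences in change are to be analysed by both Student's t test and "analysis of covariance to adjust for the baseline values". Analyses are run on intention-to-treat and per-protocol sets, with intention-to-treat named as main. Neither of the two tests is named as main.

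The Conclusions list three hypotheses. The second (adiponectin) and third (vascular and cardiac function) rest on secondary endpoints. The Discussion says of the vascular and cardiac benefit that it is "a hypothesis that will be tested in this trial".

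**The concern.** Two features of the stated rule matter.

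- **No deciding test.** With two tests of the same change and one threshold, a reader cannot tell what happens when one gives p<0.05 and the other does not. If either may be cited, the working significance level exceeds 5%. This reaches the primary endpoint too.
- **One label for everything.** The rule lets any single secondary metric be called statistically significant in the same terms as the primary result. The third hypothesis is the most exposed, because several carotid and echocardiographic metrics could each be read as supporting it.

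At stake is how the results are labelled and read. A chance finding on one imaging metric could be reported as a demonstrated vascular or cardiac benefit of one statin over the other.

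**Working it through.** The plan gives no family-wise error figure, so there is none to reproduce.

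**Inputs from the protocol article**

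- Threshold: two-sided 0.05 (Statistical analyses).
- Laboratory secondaries: 11, namely insulin, C-peptide, HOMA-R, HOMA-β, four lipids, adiponectin, CRP and troponin I (Measurements).
- Carotid metrics: 5 rows (Table 1).
- Echocardiography: at least 1 (global longitudinal strain), or 5 if each category in Table 1 counts once.
- Clinical events: 2 (NOD and CVD).
- Size: 250 per arm less 10% dropout = 225 per arm.

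Count: 11 + 5 + 1 + 2 = 19 at least, or 11 + 5 + 5 + 2 = 23. I use 20 as a round figure.

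**Assumptions (not in the document)**

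- Baseline to follow-up correlation r of 0.5 to 0.7.
- Uniform correlation ρ between endpoints of 0 to 0.5.
- No true difference between the arms.

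**Step 1. Error per endpoint if either test may count.** With equal variances at baseline and follow-up, scaled to 1, the change score has variance 2(1−r). The ANCOVA contrast has variance 1−r², and the covariance of the two is also 1−r². The two test statistics therefore correlate at √((1+r)/2).

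- r = 0.5: correlation 0.866, P(either |Z| > 1.96) = 7.3%.
- r = 0.7: correlation 0.922, P(either |Z| > 1.96) = 6.8%.

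A simulation of patient-level null trials (225 per arm, 3,000 replicates) agrees. Over 20 independent endpoints it gave 79% and 76.3%, which imply 1 − 0.21^(1/20) = 7.5% and 1 − 0.237^(1/20) = 6.9% per endpoint. So the figure is about 7%.

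**Step 2. All secondary endpoints, one test each.** For independent endpoints the formula is 1 − 0.95^k. For correlated ones it is the chance that at least one of k equicorrelated normal statistics exceeds 1.96 in absolute value.

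| k | ρ = 0 | ρ = 0.3 | ρ = 0.4 | ρ = 0.5 |
|---|---|---|---|---|
| 19 | 62% | 53% | 47% | 41% |
| 20 | 64% | 54% | 48% | 42% |
| 23 | 69% | 58% | 52% | 45% |

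With correlation of 0.3 to 0.8 inside a domain and 0.1 between domains, 20 endpoints give 61% to 50%.

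**Step 3. Imaging metrics behind the third hypothesis, one test each.**

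- 5 carotid + global longitudinal strain = 6: 1 − 0.95^6 = 26% at ρ = 0, and 21% at ρ = 0.5.
- 5 carotid + 5 echo categories = 10: 1 − 0.95^10 = 40% at ρ = 0, and 29% at ρ = 0.5.

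The range is 21% to 40%.

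**Step 4. Both features together.** If either test may count for each of 20 endpoints in the intention-to-treat set, the simulation gives 76–79% at ρ = 0, 66–69% at 0.3 and 53–55% at 0.5. This is an upper bound on the reading, because it treats all 20 as continuous while NOD and CVD get only a chi-square test.

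**Step 5. Adiponectin.** This is one named variable. A single between-group test of it has a 5% error rate whatever the number of other endpoints.

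**The case against.** The strongest objection is that the threshold sentence is a routine convention, and that what is really missing is a multiplicity rule, which an article may leave to a statistical analysis plan. The plan also already separates one primary endpoint from the secondaries and names intention-to-treat as main. Much of the Discussion is hedged, and the trial is presented as a step toward a larger outcome study.

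Part of this stands. The absence of an adjustment method is no fault in an article, and I do not count it. The hedging does soften the intended claims. What remains is what the text does state: an unrestricted significance label, two tests with neither put first, and secondary hypotheses that are to be tested. A later analysis plan that resolved this would have to narrow the stated rule.

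A reader might infer more than the document supports:

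- **That a false secondary finding is more likely than not.** This depends on the correlations. With one test each and 20 endpoints, the figure drops below 50% at a uniform correlation of about 0.4. Strong correlation is plausible within domains, for instance insulin with the HOMA indices, or several carotid metrics from one scan.
- **That two of the three hypotheses lack error control.** The adiponectin hypothesis does not suffer from the count, and lipids, CRP or troponin do not bear on the third.
- **That every endpoint is analysed in several ways.** NOD and CVD get only the chi-square test, and per-protocol is not the main analysis.
- **That the secondary family inflates the primary error.** It does not. Only the choice between two tests reaches the primary endpoint.
- **That the plan lets either test count.** It says both will be used and is silent on which decides. The 7% figure is conditional on that reading.

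**Conclusion.** The point holds, as a matter of a loosely stated decision rule, and should be corrected. The lack of a deciding test leaves room for about 7% error instead of 5% per change endpoint, including HbA1c. The unrestricted label gives roughly a 42% to 64% chance of at least one false significant secondary result, and 21% to 40% within the imaging metrics behind the third hypothesis. These figures rest on assumed correlations, no true difference between arms and, for the last two ranges, one test per endpoint. They exclude the per-protocol set and the additional 12-month imaging time point. The trial's primary conclusion is otherwise protected by having one endpoint at one time.

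**What to change.** Amend the Statistical analyses text in three respects:

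1. Name ANCOVA on the 24-month HbA1c change, adjusted for baseline, in the intention-to-treat set, as the single deciding test. Label the t test and the per-protocol results as sensitivity analyses.
2. Limit the term statistically significant to that test.
3. Report every secondary endpoint as a between-group estimate with a 95% CI, with any p value described as nominal and supportive.

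If the investigators want a formal claim on a secondary hypothesis, a gated sequence of named key secondaries is an option. It is a trade-off and not needed to cure the problem.

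The cost is a few sentences. The Trial status section shows the trial still recruiting, so the rule can be fixed before results are seen, which helps in an open-label trial. The downside is that fewer secondary results can be called significant.

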## Discussion

The risk of statin-induced diabetes has been found to be increased in patients receiving an intensive statin regimen and in patients with known risk factors for NOD [5, 6]. Hence, patients at high risk for developing NOD, such as patients with MetS, should be monitored carefully, particularly when high-intensity statin therapy is used. Alternatively, selective use of statins with favorable effects on glucose metabolism may represent a feasible and safe strategy for managing these patients. Given recent reports indicating neutral or beneficial effects of pitavastatin on glucose metabolism [8, 9], pitavastatin is suggested as the preferred agent. However, the current clinical guidelines do not recommend a specific statin type in populations at high risk for developing NOD [1, 27], owing to the limited data available. Specifically, most previous studies had a fixed follow-up period of 12 weeks [7, 9], allowing only for assessment of the short-term effects of statins on glucose metabolism. More importantly, to date, there have been no clinical trials specifically designed to investigate the diabetogenic effects of statins. In this regard, a randomized trial with longer follow-up is warranted, considering that the long-term effect of statins on diabetes risk is a more clinically relevant endpoint. The LESS-DM trial will provide data on whether long-term use of pitavastatin (24 months), in comparison with atorvastatin (a representative diabetogenic statin), results in protective or deleterious effects on several parameters related to glucose metabolism in the setting of MetS. Thus, the findings of the LESS-DM trial will not only confirm or refute the previous observations regarding the favorable effects of pitavastatin on glucose metabolism but also extend knowledge about the long-term effects of intensive statin treatment on NOD.

Patients with MetS seem to represent a potential target population in which diabetogenic statin use is of particular concern, given that MetS is a constellation of interrelated risk factors for not only CVD but also diabetes [28, 29]. Because preventive strategies for CVD have been found to be clinically effective and cost-effective in general high-risk populations, the importance of integrating CVD prevention efforts has also been underscored as a cornerstone for improving the prognosis in patients with MetS [30, 31]. Although lifestyle modification is the standard first-line means of preventing CVD in these patients, this is usually not enough to reach the goal recommended in general clinical practice. Pharmacological intervention using various medications is considered an alternative and practical approach for the primary prevention of CVD. Among the currently available pharmacological agents, statins have been suggested to exert protective effects against CVD development in patients with MetS [30, 32]. Specifically, several post hoc analyses of clinical trials testing simvastatin, lovastatin, atorvastatin, or rosuvastatin for primary or secondary CVD prevention have shown that statin therapy offers significant benefits to both the subgroup of patients with MetS and the entire study population [33]. However, although the primary consideration when pharmacological interventions are contemplated for patients with MetS is the prevention of CVD, the influence of these agents on diabetes risk should also be taken into account, owing to the high risk of developing NOD in this population. In particular, there is a concern that the use of statins with diabetogenic properties may reduce the potential net benefits of statin therapy in these patients. Indeed, researchers in previous studies have reported that atorvastatin or rosuvastatin therapy is associated with a greater risk of NOD in patients with MetS than in those without [34, 35]. Thus, while the clinical benefits of statin therapy fortunately exceed the hazard of developing diabetes, even in patients with MetS [35], the magnitude of the net benefit might be attenuated with the use of more diabetogenic statin types and therefore could theoretically be enhanced further with the use of less diabetogenic ones. However, there have been no previous studies assessing whether statins with less diabetogenic properties have greater beneficial effects on the cardiovascular system, particularly in individuals at high risk for diabetes, including patients with MetS. In this context, we plan to prospectively test the hypothesis that the difference in diabetogenicity between the two statin types may contribute to differences in their impacts on cardiac and vascular functions. Among several imaging parameters reflecting cardiac and vascular functions, we plan to measure left ventricular myocardial strain and carotid artery elasticity metrics in light of previous studies demonstrating the positive effect of statin use on left ventricular function [36] and carotid artery elasticity [12]. Moreover, because left ventricular myocardial strain and carotid artery elasticity metrics have been found to have prognostic values in predicting adverse clinical outcomes [37–40], it is tempting to speculate that studies comparing effects of different statins (with different diabetogenic properties) on these imaging parameters may provide useful information for inferring the potential benefits of using less-diabetogenic statins on cardiovascular outcomes until clinical endpoint data become available. Hence, the results of the LESS-DM trial will provide intriguing insight into the long-term consequences of statin-induced diabetes. Ultimately, we consider that our findings may help clinicians in selecting the most appropriate statin type for long-term treatment of patients with MetS.

Further, adiponectin has gained increasing recognition as an important antidiabetic hormone derived from adipose tissue [10, 41, 42]. Thus, the investigation of the link between statins and adiponectin may help to elucidate the molecular mechanisms underlying statin-induced diabetes. Several previous studies, albeit conducted in small numbers of patients, have demonstrated that the effects of statins on adiponectin differ according to the type of statin used [10]. Of note, in these studies, increases in the plasma adiponectin levels were relatively consistent and almost exclusively observed in patients receiving pitavastatin [43–45], whereas the adiponectin levels were unchanged or even decreased in those treated with other statin types, including atorvastatin [17, 46–48]. These findings suggest that the adiponectin-increasing effect of pitavastatin might be causally related to its neutral or favorable impact on glucose metabolism. The LESS-DM trial results will shed light on the potential link between the statin type and diabetogenicity by assessing the continuous changes in the adiponectin levels and the relationship between these changes and several glucose metabolism parameters. Considering that hypoadiponectinemia is a main contributor to MetS [49–51], patients with MetS are an appropriate study population for assessing the adiponectin-increasing effect of statins. Additionally, some studies have suggested that adiponectin per se may be protective against arterial stiffness [52, 53] and left ventricular systolic dysfunction [54, 55]. Taken together, it can be speculated that the use of statins with positive effects on the adiponectin level might have more beneficial impacts on the vascular and cardiac functions in patients with MetS, as compared with other statins, a hypothesis that will be tested in this trial.

### Strengths and weaknesses

To date, there have been few head-to-head trials comparing the effects of different statins on glucose metabolism. Therefore, our study has an advantage in this respect because we will directly compare the effect of pitavastatin with that of atorvastatin, one of the most widely used statins clinically, on glucose metabolism and NOD. Another strength of this study is the provision of information regarding the impact of statins on adiponectin, which may give insight into the potential mechanisms underlying the difference in diabetogenic properties according to the statin type. This study also has an advantage in that it will include analyses of the effects of statin therapy on imaging surrogate markers, such as carotid elasticity metrics and echocardiographic parameters. On one hand, the results of these analyses will address the question whether the use of less-diabetogenic statin types has more beneficial effects on vascular and cardiac functions in patients at high risk for diabetes. On the other hand, the major limitation of our study is that the sample size is relatively small to detect differences in clinical outcomes, such as NOD or cardiovascular events, between the groups. To mitigate this limitation, we plan to use imaging surrogate endpoints, which may allow for a smaller sample size and a shorter study duration than clinical endpoints and thereby enable the assessment of the potential benefits of pitavastatin on cardiovascular outcomes. However, we should acknowledge that this approach based on imaging surrogate indicators cannot be fully applied to NOD. Another limitation is a lack of power to perform reliable subgroup analyses based on relevant variables. For example, given that age is a major risk factor for diabetes, subgroup analyses looking at narrower age ranges will provide additional valuable information on potential age group differences in the risk of statin-induced diabetes. Large clinical trials need to be conducted to determine which age group is the most susceptible for developing statin-induced diabetes or most benefits from the use of less-diabetogenic statins. With regard to gender, although there are no direct data on gender differences in the association between statin use and NOD, some previous studies suggested that diabetogenic potential of statins might be gender-specific by demonstrating that the baseline level of adiponectin and the effect of statins on adiponectin could be different between males and females [56, 57]. Further trials with adequate numbers of males and females are required to be able to answer the diabetogenic potential of statins based on gender differences. We should also acknowledge that the influence of previous statin use on the study endpoints cannot be completely excluded, even though we will exclude patients with a history of statin exposure within 1 month before enrollment and thus will perform stratified randomization according to the previous use of statins. Finally, patients receiving some antihypertensive agents with potential to affect glucose metabolism, such as thiazide-type diuretics, β-blockers, angiotensin-converting enzyme inhibitors, and angiotensin receptor blockers, which may be important covariates, can be included in our study [58]. If these covariates are not evenly distributed between study groups despite randomization, we will perform adjusted analysis in this randomized controlled trial to correct for the imbalances in covariates.
